### Assessments

#### Psychometric assessments

##### Medical history questionnaire (screening)

Participants are asked to indicate the following: sex; age; handedness; years of education; occupation; previous episodes of head injury with loss of consciousness; current medication and dosage history; other substances currently being taken; prior experience with EEG/NIRS; for female participants, pregnancy and oral contraceptive information. This questionnaire is used to identify inclusion and exclusion criteria.

##### ADHS-Selbstbeurteilungsskala (ADHS-SB; screening and evaluation of outcome)

The ADHS-SB is a 22-item sub-scale questionnaire of the “Homburger ADHS-Skalen für Erwachsene” (HASE, [59]). The self-report questionnaire assesses the current ADHD symptoms (according to the 18 diagnostic criteria for ADHD listed in the DSM-IV and ICD-10-R) on a 0 to 3 Likert-Scale. This questionnaire is used to identify inclusion criteria and treatment effects on ADHD symptoms over time.

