## Methods/Design

In this proof-of-principle study, a total of 60 adult participants diagnosed with ADHD (combined, hyperactive, or inattentive type) are randomly blockwise assigned to SCP, NIRS, or electromyogram (EMG) feedback groups (n = 20 each) stratified for age, sex, and educational level. This is the first study to investigate and compare the efficacy of these treatment modalities in an adult ADHD population.

Twenty healthy controls matched for age, sex, IQ, and pre- and post-treatment duration will be included in the neurophysiological assessments for pre- and post-treatment measurement in order to establish “expected” activation patterns and allow for a more thorough interpretation of changes following the neurofeedback treatment. The study objectives are as follows:Assess whether there are physiological differences (EEG and ERP) in ADHD participants compared to healthy controls.Assess whether adult participants are able to demonstrate learning of cortical self-regulation.Assess whether treatment leads to an improvement in cognition (that is, attention and working memory) and behavior (that is, restlessness and impulsivity), and changes in specific EEG or NIRS parameters.Assess whether specific methods and protocols are more efficacious in changing behavioral, cognitive, and EEG and NIRS outcome variables.Assess whether changes are stable at the 6-month follow-up.Assess whether specific methods and protocols differ in the stability of cortical self-regulation and clinical effects at the 6-month follow-up.Assess whether the efficiency of the different training protocols differs depending on individual neurocognitive baseline parameters (for example, frontal lobe activation during neuropsychological assessments; baseline CNV etc.).

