### Study flow

At baseline/pre-treatment, participants are screened and diagnosed with ADHD, assessed with a battery of neuropsychological questionnaires for evaluation of cognitive and behavioral outcome variables, and evaluated using a 22-channel NeXus-32 (Mind Media B.V. with Biotrace^+^ Software, Herten, The Netherlands) continuous EEG recording (eyes closed, eyes open, auditory oddball, and auditory Go/NoGo task). Moreover, concentration changes of O_2_Hb and HHb during three executive functioning tasks (working memory, Go/NoGo, and word fluency) are measured by a 52-channel continuous wave NIRS-system (ETG-4000, Hitachi Medical Co., Tokyo, Japan). At mid-treatment (that is, after 15 sessions), post-treatment (after 30 sessions), and 6-month follow-up, the neuropsychological assessments are repeated.

Healthy controls (n = 20) undergo the EEG/NIRS assessment for the pre- and post-treatment measurement points. See Figure 1 for an illustrated overview of the study flow.

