### Inclusion and exclusion criteria

Participants include adults 18 years and older who meet the following inclusion criteria (please see “Assessments” section below for an explanation of all abbreviations):Attention Deficit Disorder inattentive type or hyperactive type or combined type according to DSM-IV criteria (ADHS-SB ≥18; WURS-K ≥30; WRI = adult ADHD).No additional serious physical, neurological, or psychiatric disorders with the exception of moderate depression (BDI-II score <28) and personality disorders, however, antisocial (SCID-II) or borderline personality disorders (BSL-23 ≤ 47) were excluded.Full scale IQ >80. 

Participants are excluded based on the following:Self-reported diagnosis of the following current symptoms: Serious physical illness or chronic diseases such as lung disease, heart disease, diabetes, hypertension, and rheumatic diseases; neurological disorders including Parkinson’s disease, stroke, multiple sclerosis and epilepsy; or indicated psychiatric disorders including bipolar disorder, psychosis, obsessive-compulsive disorder, chronic tics, Tourette syndrome, and suicidal behavior.Previous participation in another neurofeedback study.

The initial screening is conducted via phone and questionnaires are mailed to check for the inclusion criteria. The ADHD diagnostic assessment (see Table 1) will be scheduled if inclusion criteria are met. If the participants are on medications such as any short-acting stimulants, they are asked not to take them for at least 24 h prior to each assessment. For the neurofeedback treatment period, they may take their medication but on a stable dose. We do not stratify randomization for medication as we expect the usage to be very diverse.

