**Table 1 Tab1:** **List of all assessments and their respective time of acquisition**

**Visit**	**Screening**	**Pre-test**	**Treatment phase 1**	**In between test**	**Treatment phase 2**	**Post-test**	**FU test**	**FU treatment**

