### Primary and secondary endpoints

As a primary outcome, the changes in core symptoms will be assessed by the ADHS-SB (self-report) and the FEA-AFB as well as WRI (third party evaluation). Variables of secondary outcome will include cognitive factors (that is, attention, intelligence, response inhibition, and working memory) and changes in specific EEG/ERP and NIRS parameters (that is, relative and absolute power and frequency ratios, concentration changes in O_2_Hb and HHb), as well as achievement of self-regulation.

For the pre- and postevaluation, the independent variable is the treatment (SCP, NIRS, or placebo feedback). In addition, for the comparison of the neurophysiological and cognitive data the health status (healthy and ADHD participants) constitutes another independent variable.

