### Statistical analysis

#### Electroencephalogram, near-infrared spectroscopy, electromyogram and behavioral data

All dependent variables will be tested for effects within and between groups by an analysis of variance (ANOVA) (three groups x four assessment points). For the comparison of pretest-data between ADHD and healthy subjects, t-tests and/or one-way ANOVAs will be applied. If normal distribution cannot be assumed, non-parametric tests will be used.

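### The only pre-treatment ADHS-SB score is the score used to admit patients, so the planned within-group time tests include regression to the mean; the between-arm contrasts do not.

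*Protocol article*

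**What the plan says.** Inclusion and exclusion criteria sets the entry rule: "ADHS-SB ≥18; WURS-K ≥30; WRI = adult ADHD". The ADHS-SB paragraph under Assessments gives the scale a second role: "This questionnaire is used to identify inclusion criteria and treatment effects on ADHD symptoms over time". Primary and secondary endpoints makes it a primary outcome, analysed as change: "As a primary outcome, the changes in core symptoms will be assessed by the ADHS-SB (self-report) and the FEA-AFB as well as WRI".

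Table 1 (where the scale appears as ADHD-SB) marks it at screening, in-between test, post-test and follow-up test. Its pre-test cell is empty. Study flow treats screening as part of the baseline stage: "At baseline/pre-treatment, participants are screened and diagnosed with ADHD". Participants and recruitment adds that questionnaires are mailed to check the inclusion criteria and that the diagnostic assessment is scheduled only if they are met.

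For the analysis, "All dependent variables will be tested for effects within and between groups" in an ANOVA of three groups by four assessment points. One of the objectives under Methods/Design is "Assess whether treatment leads to an improvement in cognition" and in behaviour. Control group says that the healthy controls are measured twice without treatment in between. No untreated group of patients is planned.

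**The concern.** A questionnaire score is a stable level plus error. Admitting only people at or above a threshold favours those whose error happened to be positive that day. At the next measurement the error is drawn afresh and the group mean falls, whether or not anyone was trained. If the admitting score is also the first point of the time course, that fall is counted as change under treatment.

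The inference at risk is the time effect, in one arm or across all 60 patients. If the arms did not differ but ADHS-SB fell in all of them, the objective on improvement invites the reading that every training works, and part of that fall could come from selection alone. The healthy controls cannot serve as a check, because they were not selected for a high ADHS-SB and so do not show the regression expected in patients.

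**Working it through.** **1. Is the screening score the baseline?** The ANOVA has four assessment points. The ADHS-SB row of Table 1 has exactly four marks, and the first is screening, so the counts agree only if screening is the first point. The empty pre-test cell does not look like a fault in reading the table: the sleep questionnaire, PANAS, EEG and NIRS rows do carry a pre-test mark.

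**2. The plan's own figure.** Inputs from Sample-size calculation: effect size 0.81, one-sided α 0.05, power 80%. A two-sample t-test needs 19.56, so 20 per group, with power 80.8% at n = 20. The stated figure reproduces. It concerns a between-group difference, so the present point does not touch it.

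**3. Size of the artificial fall.** Inputs: the cut-off of 18 from the protocol. The applicants' mean and SD and the retest reliability r are not given and are assumed. With normal scores, no true change and independent errors,

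fall = (1 − r) × SD × φ(a) / [1 − Φ(a)], with a = (18 − mean) / SD.

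- Cut-off at the applicant mean (a = 0): φ/(1 − Φ) = 0.399/0.5 = 0.798. The fall is 0.3 × 0.798 = 0.24 SD at r = 0.7 and 0.1 × 0.798 = 0.08 SD at r = 0.9.
- Cut-off 1 SD below the mean (a = −1): 0.242/0.841 = 0.288. The fall is 0.3 × 0.288 = 0.09 SD at r = 0.7 and 0.1 × 0.288 = 0.03 SD at r = 0.9.

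In scale points, an applicant mean of 18 with SD 10 and r = 0.7 gives 0.3 × 10 × 0.798 = 2.4 points. A mean of 26 with SD 8 and r = 0.9 gives 0.1 × 8 × 0.288 = 0.2 points.

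**4. Effect on the time test.** Scores on four occasions were simulated under the same model, with selection on the first occasion only and no true change. The four-occasion F-test for time was applied at nominal 5%, r from 0.7 to 0.9.

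| Cut-off relative to applicant mean | One arm, n = 20 | All 60 pooled |
|---|---|---|
| 1 SD below, up to the mean | about 5–26% | about 8–71% |
| 1.5 to 2 SD below | about 5% | about 5–6% |

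The ends of these ranges carry simulation error of about one percentage point. A single screening-to-next-visit t-test, one-sided at 5%, concentrates on the affected step and inflates more: about 9–41% at n = 20 and 13–81% at n = 60, for applicant means of 18 to 26 and SDs of 8 to 10.

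**5. Between-arm contrast.** Comparing change between two arms of 20 under the same selection gave a two-sided error of 4.5–5.7% at nominal 5%. All arms pass the same cut-off, so the expected fall is equal and cancels.

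**The case against.** The strongest reply is that the trial's claim rests on a comparison of arms. The Discussion ties the payoff to superiority over the control condition, the EMG arm is there to separate specific from nonspecific effects, and the sample size is set for that contrast. Regression to the mean cancels there. This stands. A reader might infer that the superiority test is biased or the trial undersized; the documents support neither. The reply does not reach the within-group tests, which the protocol plans expressly alongside an objective on improvement.

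Second, the size is assumed. The protocol gives no applicant mean, SD or reliability, and if most applicants score well above 18 the effect is negligible. Selection also involves WURS-K and the WRI diagnosis, which the model ignores. This stands too: the direction is fixed, the size is not.

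Third, a fresh baseline does not make within-arm change a test of efficacy. In an unblinded trial without untreated patients it still mixes expectancy, nonspecific effects and time. That is right, and it is why the change in analysis comes first in the fix.

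Two further inferences go too far. One is that the regression of treatment success on baseline neurophysiology is biased: an average fall common to all goes into the intercept, and no bias in the predictor slopes is shown. The other is that the figures above carry over to FEA-AFB and WRI. Both are used for inclusion and have no pre-treatment value other than screening, but no numeric cut-off is stated for either and WRI has only three occasions, so for them the concern is qualitative.

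**Conclusion.** The point holds for within-group change in ADHS-SB. The admitting score is the analysis baseline, so the time effect is biased towards improvement and nothing in the design reveals by how much. Under the stated assumptions the bias ranges from barely visible to a clear excess of false positives, largest when all 60 patients are pooled and the cut-off lies near the applicant mean. This rests on normal scores, independent errors between visits and selection on ADHS-SB alone. The SCP and NIRS versus EMG comparisons and the figure of 20 per group stand. It is an inexpensive improvement to the plan and does not undermine its main comparison.

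**What to change.** 1. Under Statistical analysis, state that efficacy conclusions rest on between-arm contrasts of post-treatment ADHS-SB adjusted for the baseline score, and that within-arm change is reported as description. This needs no new data and covers patients already enrolled.
2. For participants still to be enrolled, have the ADHS-SB completed at the existing pre-test visit, where the sleep questionnaire and PANAS are already filled in, and use it as the analysis baseline. Keep the screening score for eligibility, and as the covariate where no pre-test score exists.

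The cost is a small amendment, a few minutes per participant and a mixed baseline, since Trial status says the study is ongoing. The repeat score removes the selection effect fully only if errors are independent between visits; if symptom fluctuations persist, some regression remains. It does not remove expectancy or time effects from within-arm change, so the second step is no substitute for the first.

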##### Beck’s Depression Inventory (BDI-II)

The BDI-II is a 10-minute self-reported questionnaire assessing depression symptoms during the previous two weeks [60]. This questionnaire is used to determine inclusion and treatment effects on comorbid symptoms of depression over time.

##### Borderline Symptom Liste - Kurzform (BSL-23)

The BSL-23 is a 23-item self-report questionnaire used to assess borderline personality disorder symptoms on a 0 to 4 Likert-Scale [61]. This questionnaire is used to determine inclusion and treatment effects on comorbid symptoms of borderline over time.

##### Culture Fair Test-20 Revised (CFT-20-R; screening and follow-up)

The CFT-20-R is a nonverbal intelligence test [62]. This test is used to determine inclusion and treatment effects over time.

##### Edinburgh Handedness Inventory (EHI; screening)

The Edinburgh Handedness Inventory is a self-rated questionnaire that assesses right or left hand dominance for ten activities [63]. This inventory is used for assessments.

##### Fragebogen zur Erfassung von ADHS im Erwachsenenalter, aktuelle Probleme/frühere Probleme - Fremdbeurteilung (FEA-AFB, FEA-FFB; screening and evaluation of outcome)

The FEA-AFB and FEA-FFB are third-party questionnaires designed to evaluate current (FEA-AFB) as well as childhood (FEA-FFB) ADHD-related problems and symptoms for adult participants completed by a spouse, family member, close friend or employer [64]. These questionnaires are used to determine inclusion and treatment effects on third-party rated ADHD symptoms over time.

##### Fragebogen zur Erfassung relevanter Therapiebedingungen (FERT; evaluation of outcome)

The FERT is a self-rated questionnaire to assess relevant treatment conditions, patient expectations, and patient-therapist interactions [65]. This questionnaire is used to assess treatment expectation as a nonspecific variable.

##### Structured Clinical Interview for DSM-IV Disorders (SCID-I; SCID-II; screening)

The SCID is a semi-structured interview for the assessment of DSM-IV disorders [66]. This interview is used for inclusion and exclusion criteria.

##### Test d2- Revision Aufmerksamkeits- und Konzentrationsstest (d2-R; screening and evaluation of outcome)

The d2-R is a 10-minute assessment in which participants cross out the target letter from a series of similar letters [67]. The total number of items processed minus errors indicates combined speed and accuracy scores for attentional and inhibitory control. This test is used to assess attention in comparison with healthy controls and for treatment effects over time.

##### Wender-Reimherr Interview (WRI; screening and evaluation of outcome)

The WRI is the structured interview of the sub-scale of the HASE [59]. The interview investigates psychopathological characteristics of adult ADHD. Responses are rated on a 0 to 2 Likert-Scale. This interview is used to determine inclusion and treatment effects on third-party rated ADHD symptoms over time.

##### Wender Utah Rating Scale-Kurzform (WURS-K; screening)

The WURS-K is a 25-item sub-scale questionnaire of the HASE [59]. The questionnaire establishes a retrospective diagnosis of childhood ADHD symptoms for adult ADHD evaluation using a 0 to 4 Likert scale. This questionnaire is used to identify inclusion criteria.

##### Psychopathic Personality Inventory (PPI)

The PPI-R is a 26-item self-report measure of emotional detachment using a 1 to 4 Likert-Scale [68]. This inventory is used to identify inclusion criteria.

##### Schlaffragebogen A

The “Schlaffragebogen A” is a 23-item self-rated questionnaire that assesses sleep quality and behavior for the previous night of sleep [69]. This questionnaire is used to assess the quality of sleep before the EEG measurements.

##### State-Trait Anxiety Inventory (STAI)

The STAI is a self-rated 40-item questionnaire about temporary and long-term anxiety with a range of four possible responses to each [70]. This questionnaire is used to identify inclusion criteria and treatment effects on comorbid symptoms of anxiety over time.

##### Change of living conditions checklist

Every fifth feedback session, the participants fill in a general checklist about living conditions including changes in sleep, mood, coffee, nicotine or drug intake and any major changes in their lives. This checklist is to identify any major changes over the course of training that might lead to nonspecific treatment effects.

### Neurophysiological parameters

All neurophysiological parameters are assessed for comparison to the healthy control group and to assess changes over the course of treatment.

Quantitative EEG (QEEG) data are collected using 22 EEG channels positioned according to the international 10–20 system. Two channels of the NeXus-32 (Mind Media B.V. with Biotrace^+^ Software, Herten, The Netherlands) will be dedicated to detecting horizontal eye movements and are attached 1.5 cm lateral to the outer canthus of each eye. Two additional electrodes will be used to detect vertical eye movements and are attached 3 mm above the middle of the left eyebrow and 1.5 cm below the middle of the left lower eyelid. Study tasks include an assessment of eyes closed and eyes open resting state, auditory oddball, and auditory Go-NoGo task. The resting state assessment will consist of an 8-min alternating eye open (1 min)/eyes closed (1 min) asymmetry task, 15-min eyes-closed recording, directly followed by a 5-min eyes-open recording. We will analyze absolute and relative power for the delta (1.5-3.5 Hz), theta (3.5-7.5 Hz), alpha (7.5-12.5 Hz), and beta (12.5-25 Hz) frequency bands and calculate asymmetry, coherence, alpha peak frequency, EEG phenotype, and EEG vigilance stage changes. The variables will be used to assess differences between the adult ADHD and health control participants at baseline, as well as the pre- and post-training effects in the ADHD participants.

### Auditory P300 task (Go/NoGo-oddball task)

An auditory oddball task with three different tones (see [71]) is used to elicit P3a and P3b components to investigate inter alia attentional resources for stimulus evaluation. Participants have to press a response button whenever they hear the previously defined target tone (N = 60, 1500 Hz) in a 10.5-min paradigm with additional standard tone (N = 359, 1000 Hz) and a less frequent distractor tone (N = 60, white noise). The three stimuli are presented in a pseudo-randomized order (presentation time: 50 ms; interstimulus-interval: 1300 ms). P300 amplitude and latency over central, frontal and parietal electrodes will be calculated, as well as RT, RT variability and error rates.

### Auditory P300 task (oddball task)

An auditory oddball task with two different tones is used to elicit the P300 component. Participants have to silently count the deviant tone with their eyes closed. An 8.5 min paradigm with standard tone (N = 150, 1000 Hz) and a deviant tone (N = 49, 1500 Hz) will be used. The two stimuli are presented in a pseudo-randomized order (presentation time: 50 ms; interstimulus-interval: 1300 ms). At the end of the paradigm, the experimenter asks for the count and takes note. P300 amplitude and latency over central, frontal and parietal electrodes will be calculated.

### Auditory Go/NoGo task

An auditory Go/NoGo task with three different tones is used to assess cognitive preparation, attention, and impulsivity by instructing participants to press a response button whenever they hear a previously defined target stimulus (S2_target_, N = 50, 2000 Hz) that follows a warning stimulus (S1, N = 200, 500 Hz) at a variable presentation interval within a 14-min paradigm. All three stimuli are presented in S1-S2 or S1-S2_target_ segments. Each tone is presented for 50 ms; the duration of each segment lasts 1800 ms. The segments are presented in a pseudo-randomized order with an interstimulus-interval of 2000 to 2400 ms. The CNV amplitude over central and frontal electrodes will be calculated as well as the RT, RT variability and error rate.

### Measures of peripheral physiology

Electrocardiogram (ECG), skin conductance level (SCL) and respiration measures are simultaneously and continuously recorded using the Nexus 32 system (Mind Media B. V., Herten, The Netherlands). ECG electrodes are placed on the participants’ chest (reference/ground below right and left clavicle and the active electrode below left-side ribcage) and used to assess heart rate and heart rate variability measures. A Velcro-elastic respiration band is placed around the participants’ waist or chest, based on comfort and signal quality. Finally, the SCL sensors are fixed to the participants’ nondominant hand with Velcro-sensors. The peripheral data from heart rate, respiration and SCL will be used to assess the peripheral arousal during active (ERP tasks) and resting (eyes open/eyes closed) conditions.

